### Statistical analysis

#### Sample size

To detect the clinically relevant difference in the dementia rate after the hearing aid fitting compared with the health education group, the sample size of this study is calculated as follows. Our pilot study results showed that 3 of 30 patients with ARHL and MCI wearing hearing aids developed dementia within a year. Literature reported that 18% of the elderly with MCI progressed to dementia every year [73]. In conclusion, by using PASS software (Vision 15), *α* was set at 0.05, 1 – *β* = 0.8, and hearing aid fitting and health education group were set at 1:1; thus, 292 cases in each group were calculated. Considering the 15% of drop-out rate, we designed 344 cases in each group, and a total of 688 cases. Shanghai Ninth People’s Hospital will be responsible for 516 cases, Shanghai Sixth People’s Hospital for 103 cases, and Shanghai Ruijin Hospital for 69 cases. Furthermore, Shanghai Mental Health Center will provide training about cognitive evaluations for our researchers and recommend eligible patients for our study.

#### Data collection

All research centers will use the paper Case Report Form designed for the study to record the original data. Then, they will be input into the Shen-kang Clinical Research Integration Platform system by trained researchers from Shanghai Ninth People’s Hospital. The database is password-protected, which can only be accessed by specified researchers. All changes made in the database will be logged. The final data set will be only available to authors for research.

The research centers will utilize the designated paper Case Report Form (CRF), specifically designed for this study, to record the original data. Subsequently, trained researchers from Shanghai Ninth People’s Hospital will input the data into the Shen-kang Clinical Research Integration Platform system. Access to the database is protected by a password and limited to authorized researchers. Any modifications made within the database will be meticulously logged. The final dataset will solely be accessible to the authors for research purposes.

#### Statistical methods

The mean and standard deviations, or the median and quartiles, will be used to describe the baseline features of both the hearing aid fitting group and the health education group, depending on the normality of the data. The unpaired *t*-test will be used to calculate the differences between the control and intervention groups. For within-group comparisons, paired *t*-tests will be used for continuous measures. Non-parametric tests will be used to compare data that do not follow a normal distribution. The differences in outcomes between groups will be determined by calculating the means and 95% confidence intervals. A *P* value < 0.05 will be considered statistically significant. Additionally, mixed effects models, COX regression, and multifactorial linear regression will be utilized to further explore the association between hearing aid fittings and cognitive improvement.

Intention-to-treat analysis will be conducted on all subjects enrolled in the group. Additionally, a per-protocol analysis will be performed on subjects with high compliance, specifically those who have worn hearing aids for the duration required by the experiment. To handle missing data, multiple imputation will be utilized. Complete case analyses will be conducted as a sensitivity analysis. It is important to note that all analyses will be performed on an intention-to-treat basis.

We will perform an interim analysis when all subjects complete the 12-month follow-up visits using the baseline data and follow-up data collected at 6 and 12 months after the interventions, and if the results of the interim analysis are positive, we will consider terminating the study.

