### Intervention

After randomization, every participant allocated to the hearing aid fitting group will get the binaural and behind-the-ear hearing aids, Widex-Evoke E-FA100 & E-FP50, with a full set of auxiliary accessories, purchased by Ninth People’s Hospital and distributed to each sub-center. Our professional audiologist will make adjustments for patients until they can hear what others say with a few noisy environmental sounds, which will make participants willing to learn the usage of hearing aids and wear them in their daily lives. In addition, some of the subjects with a long history of hearing loss may lead to poor effect of hearing aids. We will provide some suggestions on hearing rehabilitation for them, including reading newspapers out and talking to their families frequently. Patients are required to wear hearing aids for more than 10 h per day. The time of wearing hearing aids will be recorded by a system; thus, we can remind subjects. Furthermore, participants will maintain their hearing aids if needed and make regular adjustments to their hearing aids with the help of an audiologist.

The patients in the health education group will receive periodic health education from researchers as part of the study, including valuable guidance on hearing health, such as the importance of noise reduction, avoidance of ototoxic drugs, and development of healthy ear care habits.

Furthermore, we will make it clear to the participants that those who are allocated to the intervention group will benefit from using hearing aids free of charge for the rest of their lives, while those who are assigned to the control group will receive an extra allowance at the end of the trial period. Besides, in the hearing aids group, we will use the system in hearing aids to record the average duration of hearing aid use, and for those who do not meet the requirement, we will take measures such as the commissioning of hearing aids and online supervision. All participants will get subsidies for the cost of transportation for every follow-up visit.

In the follow-up stage, the patients of the two groups will be recalled to study centers to perform assessments of auditory tests and cognitive evaluations at 6, 12, and 24 months after the intervention. Researchers will contact those who are near the date of the follow-up visit and make an appointment with them in advance.

Subjects are not allowed to participate in another trial which may influence the results during the study.

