#### Primary outcome measure

The primary outcome of the study is the rate of patients with ARHL and MCI progressing to dementia in two groups after different interventions.

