### Blinding

Blinding is not possible in this study due to the nature of the intervention for participants or researchers, but we intend to blind the data analyzers to reduce bias in the data analysis. Moreover, we will employ several strategies to mitigate bias from both researchers and participants. Firstly, prior to their involvement in the CHOICE project, researchers will receive standardized training to ensure consistent data collection and analysis. Additionally, we will utilize standardized measurement tools and quality control procedures to monitor data accuracy and reliability. Furthermore, we will ensure that participants in both the intervention and control groups are well-informed about the potential benefits and drawbacks of their respective treatments, aiming to minimize biases in their perceptions of therapeutic effects.

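### The one sensitivity analysis named for missing data, complete-case, does not test drop-out caused by dementia that arises after the last attended visit

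*Protocol article*

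**What the plan says.** The Statistical methods section of the protocol article fixes the approach in two sentences: "To handle missing data, multiple imputation will be utilized. Complete case analyses will be conducted as a sensitivity analysis". It names no other sensitivity analysis for missing data. The same section adds that "a per-protocol analysis will be performed on subjects with high compliance", but that analysis concerns hearing-aid wear time, not absent outcomes. The section on participants' withdrawal says that losses will be recorded and gives no assumption about why they occur.

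Other sections set the context:
- Primary outcome measure: "The primary outcome of the study is the rate of patients with ARHL and MCI progressing to dementia in two groups".
- Sample size: "Considering the 15% of drop-out rate", 292 per arm becomes 344 per arm.
- Blinding: "Blinding is not possible in this study due to the nature of the intervention for participants or researchers".
- Intervention: outcomes are collected by recalling participants to the centres at 6, 12 and 24 months. The hearing-aid arm keeps its devices free for life, while "those who are assigned to the control group will receive an extra allowance at the end of the trial period".

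**The concern.** A sensitivity analysis should relax the doubtful assumption of the main analysis. Standard multiple imputation assumes that, given the data in the imputation model, those who leave have the same dementia risk as those who stay. Complete-case analysis makes a similar or stronger assumption, so it does not relax the doubtful one.

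The assumption is open to doubt here because the outcome is itself a plausible reason for not attending. Dementia status is learned at a clinic visit, and a participant whose dementia emerges between visits may not return. Everything recorded for that person then predates the event.

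Agreement between the two analyses could therefore be reported as robustness when the relevant departure was never examined. The Statistical methods section also allows termination to be considered if the 12-month interim analysis is positive, so a fragile result could carry weight early.

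**Working it through.** **Inputs from the Sample size section.** Control rate 18% per year; hearing-aid rate 3/30 = 10% in a year; alpha 0.05 (taken as two-sided, which reproduces the plan's figure); power 0.80; 1:1 allocation; 292 per arm; 15% drop-out; 344 per arm.

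**Assumed, because the article gives no figure.** The factor k by which the odds of dementia in drop-outs exceed those in completers, and its pattern across arms.

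**1. The plan's own figure.** With unpooled variance, n = (1.960 + 0.842)² × (0.18×0.82 + 0.10×0.90) / 0.08² = 7.849 × 0.2376 / 0.0064 = 291.4, so 292. Then 292/0.85 = 343.5, so 344. Both figures reproduce. About 344 − 292 = 52 participants per arm are expected to be missing. The design difference is 0.08 × 292 ≈ 23 events.

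**2. False-positive rate with no true effect (18% v 18%).** Control drop-out is unrelated to dementia. In the hearing-aid arm the completer risk c and drop-out risk r satisfy 0.85c + 0.15r = 0.18 and r/(1−r) = k·c/(1−c). With SE = √{[c(1−c) + 0.18×0.82]/292} and z = (0.18 − c)/SE, the rejection rate is Φ(z−1.96) + Φ(−z−1.96).

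| k | c | r | Apparent benefit | SE | z | Rejection rate |
|---|---|---|---|---|---|---|
| 1 | 0.180 | 0.180 | 0 | 0.0318 | 0 | 5% |
| 2 | 0.1624 | 0.2795 | 0.0176 | 0.0312 | 0.56 | 9% |
| 3 | 0.1505 | 0.3471 | 0.0295 | 0.0307 | 0.96 | 16% |
| 4 | 0.1416 | 0.3975 | 0.0384 | 0.0304 | 1.26 | 24% |

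**3. Other patterns.** With the same k in both arms under the null, c is the same in both arms, the difference is zero and the rate stays at 5%. For a true 10% v 18%, let demented participants be m times as likely to drop out. The observed rate is p(1 − m·q)/0.85 with q = 0.15/(p·m + 1 − p).
- m = 2 or 3 in both arms: the difference shrinks from 8.0 to 7.2 or 6.8 points.
- m = 3 in controls only: the control rate reads 14.2%, the difference is about 4.2 points, and power falls from 80% to about 33–35%.

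**4. Does imputation give a warning?** A simulation of 3,000 trials took 14% v 14% with m = 2, 3 or 4 in the hearing-aid arm only. Complete-case showed a false benefit of 1.9, 3.3 or 4.5 points, and imputation by arm 1.8, 3.2 or 4.4. The two estimates correlated at 0.99. That imputation model held only one binary baseline predictor, so it shows what happens when the model says little about the later course. A model using the 6- and 12-month visits would remove part of the bias and could differ visibly from complete-case.

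**5. Tipping point for the design result.** For an observed 10% v 18%, SE = √[(0.10×0.90 + 0.18×0.82)/292] = 0.0285, z = 2.80 and p = 0.005. Keep control drop-outs at 18% and hold the SE. Significance is lost when 0.18 − (0.85×0.10 + 0.15r) = 1.96 × 0.0285 = 0.0559, so r = 0.0391/0.15 = 0.26. In odds against completers this is (0.26/0.74)/(0.10/0.90) ≈ 3.2.

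Delta-adjusted imputation on similar data (29/292 v 53/292, 52 missing per arm) agrees. Complete-case and unadjusted imputation both give p = 0.004. Multiplying the hearing-aid odds by 2, 2.5, 3 and 4 gives p = 0.019, 0.032, 0.053 and 0.099, so the result tips at about 3, an imputed rate near 25%. A weaker result (29/292 v 47/292) starts at p = 0.025 and tips at about 1.5 (p = 0.053).

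**The case against.** The strongest reply is that this is a condensed article. The full protocol and any SAP are not shown, and imputation models, delta ranges and tipping points commonly belong there. The article does not say that complete-case will be the only sensitivity analysis, and imputation with a complete-case check is neither a misstatement nor a contradiction. This limits the point but does not remove it: the article states which check it will use, and that check does not address the main threat to this outcome. An unseen document may add a better one.

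Four stronger readings are tempting, and the documents do not support them.
- A reader might infer that the two analyses must agree whatever happens. They need not: with 6- and 12-month data in the imputation model they can diverge when drop-out depends on what was seen at those visits.
- A reader might infer false-positive rates of 36% or 58%. These arise if hearing-aid drop-outs have 2.5 or 3 times the average risk, that is 45% v 13.2% or 54% v 11.7% in completers. The odds ratios are then about 5.4 and 8.9, beyond the 1 to 4 range proposed here for examination.
- A reader might take the open label and the unequal incentives as evidence that dementia drives drop-out more strongly in the hearing-aid arm. They make differing drop-out rates plausible. They do not show differing dependence on dementia, which is what a false positive needs in these calculations.
- A reader might infer that dementia status will be imputed after death. The article never says that death counts as missing data.

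It is also fair to say that a design-like result tipping only near an odds ratio of 3 is moderately robust. A trial reporting that figure would strengthen its case.

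**Conclusion.** The point holds in limited form. The named check does not test drop-out caused by dementia that arises after the last attended visit, although it can respond to drop-out that depends on observed earlier visits. At 15% drop-out per arm and no true effect, dependence confined to the hearing-aid arm raises the complete-case false-positive rate from 5% to about 9%, 16% or 24% at odds multipliers of 2, 3 or 4. Dependence confined to controls would hide a real effect. A design-like 10% v 18% loses significance at an odds multiplier of about 3.

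The conclusion rests on standard (missing-at-random) imputation, which the article implies but does not state, and on assumed multipliers. The change should be made, with medium confidence about how much it would matter in practice. The sample size is not in error.

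**What to change.** 1. Keep multiple imputation as the main approach. Run it within arm, with the 6- and 12-month cognitive assessments (for example CDR and ADAS-Cog, where collected) in the model.
2. For the primary outcome, make the sensitivity analysis a delta-adjusted (pattern-mixture) imputation. Multiply the odds of dementia among the missing by values from 1 to 4, separately in each arm, and report the tipping point at which the conclusion changes.
3. Keep complete-case results as description only.
4. Settle the wording before the 12-month interim analysis.

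The cost is about a paragraph of text and some programming, with no new data. The downside is that the robustness statement may look less favourable than agreement between imputation and complete-case would.

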### Quality control

Researchers, including audiologists, cognitive evaluators, and data collectors, will be required to ensure full compliance with specifications and pass the consistency test during the assessment process. Additionally, 5% of the subjects will be randomly selected for audio recording of the entire cognitive evaluation process, which will be submitted to the Shanghai Mental Health Center for quality control.

An external data monitoring committee will monitor the study. The committee will be independent of the sponsor and researcher in the study and have no competing interests. The committee will have an audiologist, a psychiatrist, and a statistician, who will review the provisional data when the completion of data collection for the first year. The implementation of projects will be tracked and reviewed by the Ethics Committee of Ninth of Shanghai Ninth People’s Hospital every year.

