### Ethics and dissemination

All subjects will participate in the study voluntarily, and the senior researchers in our project team, such as [name], [name], [name], [name], [name], [name], [name], [name], will obtain their written consent forms from each individual prior to their enrolment in the group. It is expected that both groups of subjects will derive benefits from the study. Additionally, we will inform all participants about any new information that may influence their willingness to participate in the experiment. The trial will adhere to the criteria and principles outlined in the Declaration of Helsinki and has received approval from the Ethics Committee of Shanghai Ninth People’s Hospital (project ID: ChiCTR2000036139) [74]. We will also be subject to an annual ethical review. Furthermore, we have registered the trial on chictr.org.cn. Any modifications to the study will be promptly communicated to the Ethics Committee of the Ninth Hospital and will be updated on the registration website once approval is obtained.

The entirety of the research-related data, including original data and records, quality control files, and software used for data storage and follow-up analysis, will be limited to access by the study team only. The statistical analysis and processing of the collected data will be conducted exclusively by designated researchers. The identity and contact information of all participants will be strictly confidential. Prior to performing statistical analysis, the data will be anonymized. Ultimately, the research findings will be published in reputable scientific journals.

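### The protocol does not reconcile who sees and acts on the 12-month between-arm result: the study team runs it and decides, data access is confined to the team, yet an external committee reviews the same data

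*Protocol article*

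**What the plan says.** Five statements in the protocol article bear on this point.

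- **Statistical methods.** The team runs the look: "We will perform an interim analysis when all subjects complete the 12-month follow-up visits". The team also acts on it: "if the results of the interim analysis are positive, we will consider terminating the study". The external committee is not mentioned here.
- **Quality control.** "An external data monitoring committee will monitor the study". It is independent of sponsor and researchers, includes a statistician, and has members "who will review the provisional data when the completion of data collection for the first year". No recommending or deciding role is given to it.
- **Ethics and dissemination.** All research data "will be limited to access by the study team only", and the analysis is reserved for designated researchers. Under Data collection, the database is likewise open only to authorised researchers.
- **Blinding.** "Blinding is not possible in this study due to the nature of the intervention for participants or researchers". For the analysts, however, "we intend to blind the data analyzers to reduce bias in the data analysis".
- **Cognitive evaluations.** These are done at the study centres by the project's own researchers. Visits fall at 6, 12 and 24 months.

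**The concern.** An interim comparison in an open-label trial is safest in the hands of people who do not go on to assess outcomes. This protocol already has such a body, but the section that defines the interim analysis gives both the comparison and the decision to the investigators, and the section on data access leaves the committee out.

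The stopping wording is also permissive: the team will consider termination, so a positive result followed by continuation is possible under the plan. In that case the remaining 24-month evaluations would be made by allocation-aware staff, and nothing in the article keeps the direction of the 12-month result from them. Several instruments leave room for expectation. The Clinical Dementia Rating is a graded judgement over six domains, and the daily-living and functional-activities scales rest on interviews with family members.

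At stake is the credibility of the 24-month comparison if the trial continues, and clarity about who is accountable for stopping it early. The point concerns who sees and acts on the interim result. It does not concern the significance threshold used at the look.

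**Working it through.** **Step 1: the sections side by side**

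| Question | Statistical methods | Quality control | Ethics and dissemination |
|---|---|---|---|
| Who handles the 12-month data? | The study team | External committee reviews it | Study team only; designated researchers analyse |
| Who decides on stopping? | The study team | Not stated | Not stated |
| Who is barred from the by-arm result? | Not stated | Not stated | Read literally, anyone outside the team, so the committee too |

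Read literally, the access limit and the committee's review cannot both hold. The stopping sentence and the committee's review can coexist, but nothing says how they relate.

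**Step 2: can the result reach the assessors?** The researchers are unblinded and they perform the cognitive evaluations. The interim result goes to the team. No sentence separates those who receive the result from those who assess. So it can reach them. The article does not say that it will.

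**Step 3: how many assessments are still open at the look?**

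Inputs:
- Planned total of 688 (Sample size). This reproduces. With 10% v 18%, two-sided 0.05, power 0.80 and unpooled variance, n = (1.960 + 0.842)² × (0.10 × 0.90 + 0.18 × 0.82) / 0.08² = 291.4, so 292 per arm. Then 292 / 0.85 = 343.5, so 344 per arm and 688 in total.
- First enrolment on 28 September 2021, and recruitment expected to finish by 2023 but still open in November 2023 (Time points/timeline).
- Look when the last participant reaches month 12 (Statistical methods).

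Assumptions: uniform accrual, no drop-out, and a look with no delay. At that moment, those enrolled in the final 365 days of accrual have not reached month 24. The open share is therefore 365 / (days of accrual).

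- Accrual ends 31 December 2023: 824 days. 365 / 824 = 44.3%, and 0.443 × 688 ≈ 305 participants.
- Accrual ends 30 June 2024: 1,006 days. 365 / 1,006 = 36.3%, and 0.363 × 688 ≈ 250 participants.

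Data come from paper forms that must be entered first, so some delay is likely. With the end-2023 close, a look 3 months later (91 days) leaves (365 − 91) / 824 = 33%. One 6 months later (182 days) leaves (365 − 182) / 824 = 22%.

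**Step 4: size of the bias.** This would require knowing how far awareness of the interim direction shifts a rating, over and above awareness of allocation, which the assessors have from the start. The document gives no such figure, so no bias is computed.

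**The case against.** The strongest reply is that the protections exist and only the wording is loose. Analysts are to be blinded, database access is limited to authorised researchers, data are anonymised before analysis, and an independent committee with a statistician reviews the data at the interim time point. The access limit is a general confidentiality clause, and the Data Availability statement offers datasets on request, so it is not absolute. A team that considers termination is compatible with a committee that advises. Closed reports and release rules commonly sit in a charter or a full protocol that is not shown.

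Much of this stands. The absence of detailed procedures for separating interim results from the team is no finding. Blinding the analysts helps little, however, once the result goes to the team that decides. A charter giving the committee the by-arm data and a recommending role would also not sit with the published sections as worded. The conflict lies in text that is present.

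Four stronger readings are tempting, and the document does not support them:

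- *The 24-month assessors will know which arm is ahead.* No section says they are shown the result. The text supports only that they could learn it.
- *The bias is a stated fraction of the design effect.* Any assumed rating shift would have no source in the document. Setting a shift at 24 months against the 8-point design difference would also mix time frames, because 10% and 18% are one-year rates.
- *Controls will be told and will obtain hearing aids or leave.* The article does promise that "we will inform all participants about any new information that may influence their willingness to participate in the experiment", but this is general consent wording and nothing ties it to interim results.
- *No analysis could address the problem.* On the figures above, more than half of the 24-month assessments would precede the look, so a before/after sensitivity comparison is possible.

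**Conclusion.** The concern holds as an inconsistency with a practical consequence. The sections on statistical methods, quality control, and ethics and dissemination disagree on who sees the 12-month comparison, and they do not settle who decides on stopping. Followed as written, the first and third put the by-arm result and the decision with an open-label team whose researchers still have evaluations to make.

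The exposed part is a substantial minority of the 24-month assessments: about 36% to 44% of 688 under uniform accrual ending mid-2024 or end-2023 with an immediate look, falling to about 33% or 22% in the end-2023 case if the look comes 3 or 6 months later. These shares rest on assumed accrual and ignore drop-out. They show how much data could be touched, not how large any distortion would be. The change is worth making because it is cheap and uses bodies already planned.

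**What to change.** Reconcile the three sections as follows.

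1. **Statistical methods:** the blinded data analyst prepares the by-arm interim report, and it goes only to the external data monitoring committee. The committee recommends stopping or continuing, and the study team receives only that recommendation.
2. **Quality control:** give the committee this recommending role explicitly, in place of a bare review of first-year data.
3. **Ethics and dissemination:** exempt the committee from the study-team access limit. State that by-arm interim results are withheld from outcome assessors and site staff until 24-month follow-up is complete or the trial stops.

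The cost is wording in three sections and a short committee charter. The committee, its statistician and the blinded analysts are already planned, and no participants, visits or tests are added. The downside is that investigators cannot see or publish 12-month comparative results while follow-up continues.
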